#### Concurrent sports participation and medical treatment

No restrictions will be given for both groups with regard to sport participation or concurrent medical treatment. If the athlete will experience an increase in pain in the first 48 hours after treatment he/she will be advised to take paracetamol up to a maximum dose of 3 dd 1000 mg for pain relief.

### Measurements

#### Baseline

After informed consent the following baseline measurements will be carried out:

#### Baseline questionnaire

The baseline questionnaire consists of three parts. Part 1 covers demographic variables such as name, address, age, gender, and e-mail address. Sports participation will be assessed in part 2 by using questions concerning type and level of sport and mean hours of sports participation and sport history. Information about medical history, knee injuries and previous medical treatment will be collected in the third part of the questionnaire.

#### VISA-P questionnaire

The primary outcome of the TOPGAME study is the self-reported VISA-P score [12]. The VISA-P score is a simple, reliable instrument for measuring the severity of patellar tendinopathy and is sensitive to small changes in symptoms. It was specifically designed for patellar tendinopathy, rating pain, symptoms, simple test of function and the ability to play sports. Six of the eight questions are scored on a scale from 0 to 10 points, with 10 representing optimal health. The maximum VISA score for an asymptomatic athlete is 100 points. Validity and reliability of the Dutch translation of the VISA-P score have been demonstrated recently [13].

#### VAS pain

Secondary outcome parameters are ratings of pain on a Visual Analogue Scale (VAS) during activities of daily living (ADL) and sports, and during functional tests like maximal jumping tests, triple hop test and the single leg decline squat (SLDS); the latter test, in which the athlete performs a single-leg squat to 60° of knee flexion on a 25° decline board ten times, was designed to preferentially load the patellar tendon [15,16].

#### Ultrasound

Greyscale ultrasound and Power/Colour Doppler characteristics of the patellar tendon (hypo-echogenity, diameter, calcifications, and degree of neovascularisation) will be collected by an experienced radiologist.

### Follow-up

Follow-up measurements for VISA-P and the VAS pain assessments will be carried out at 1, 12 and 22 weeks after the final treatment, when athletes are still in competition. Side effects and adverse reactions/events and the rate of overall treatment satisfaction will also be recorded. At 22 weeks after final treatment, ultrasound characteristics will be collected by the same experienced radiologist who is blinded to the athletes' group allocation. Further both groups of athletes will be recording their athletic activities and concurrent medical treatment on a weekly basis, using a web-based diary.

### Sample size

Sample size is calculated based on the VISA-P score. From previous investigations a baseline score of 64 points is expected in symptomatic athletes (95 points in athletes without patellar tendinopathy), with an SD of 19 points (2). (To our knowledge no data are available that describe the SD of the difference between the baseline and 6 month VISA-score.)

A 15-point difference in the VISA score between the treatment and placebo is considered to be clinically relevant. To detect a difference of 15 points on the VISA scale with an SD of 19, a power of 90% and an alpha of 5%, 34 subjects per group are needed.

The proposed treatment protocol without local anaesthesia and with patient-guided dosage (for pain tolerance) is chosen based on our previous experience with ESWT application in patients with patellar tendinopathy ([name], submitted). All patients tolerated this procedure well without adverse complications; therefore we do not expect a higher-than-normal drop-out rate of athletes due to pain during the treatment. Assuming a drop-out rate of about 20% this would mean that a total of 86 subjects are required at baseline (43 in each group).

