### Randomization

Volleyball, handball and basketball players with patellar tendinopathy are allocated randomly and blinded to an intervention group (patient-guided ESWT) or a control group (placebo treatment) by an independent statistician (EV) who is blinded for any baseline characteristics of the participants. Randomisation is performed before the first treatment by means of a computer-generated randomisation list (SPSS 16, Chicago, USA). The randomisation procedure takes place at team level, resulting in players from the same teams being allocated to the same group. While the different treatment methods within the study groups potentially have various immediately noticeable effects on the subjects (e.g. level of pain), this method of randomisation is chosen to keep the treatment group blinded to the subjects, and to avoid spill-over of the intervention. The independent physical therapists who administer the ESWT or placebo treatment are informed by the statistician about the group allocation. Group allocation is concealed from the athletes and the outcome assessor at all times during the trial.

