### Statistical analyses

Descriptive statistics (means and standard deviations, numbers and percentages) will be used to describe the characteristics of the intervention and control group and the outcome variables at the three measurement points. To evaluate potential group differences at the start of the study, baseline values will be analysed for differences between intervention group and control group. The effect of the ESWT treatment will be assessed using multilevel analysis. The multilevel analysis will be used to determine whether there is a difference on the primary and secondary outcome variables between the two groups over time. This statistical technique takes into account the dependency of observations of different subjects. Analyses will be adjusted for gender, age, type of sport, and baseline values of any other post hoc confounders. Analyses will be performed following the 'intention to treat' principle. Differences will be considered statistically significant at p < 0.05. All analyses will be done using SPSS version 16 (SPSS, Chicago, USA).

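### The stated 90% power comes from a formula for independent athletes, but whole teams are randomised, so the figure is not supported as written

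*Protocol article*

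**What the plan says.** The Sample size section of the protocol article states: "Sample size is calculated based on the VISA-P score". It sets the target effect: "A 15-point difference in the VISA score between the treatment and placebo is considered to be clinically relevant". The SD is 19 points, taken from earlier work on symptomatic athletes. The section adds that no data were available on the SD of the change from baseline to six months. From these inputs it concludes that at "a power of 90% and an alpha of 5%, 34 subjects per group are needed". It then allows for about 20% drop-out and arrives at 43 per group, 86 in total.

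The Randomization section fixes a different unit of allocation: "The randomisation procedure takes place at team level, resulting in players from the same teams being allocated to the same group". The reasons given are to protect blinding and to avoid spill-over.

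The Statistical analyses section plans a multilevel analysis on the ground that it handles dependency between subjects. The criterion is: "Differences will be considered statistically significant at p < 0.05".

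**The concern.** Three sections do not fit together. Allocation is by team and the analysis allows for dependent subjects, but the sample size treats each athlete as independent. When players of one team share an arm and their outcomes are positively correlated, the treatment comparison has a larger variance than the two-sample formula assumes. The multilevel model will carry that extra variance; the sample size does not.

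The article's condensed form does not explain this. The section gives every input, and the stated numbers leave no room for an allowance made elsewhere.

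What is at stake is how a null result is read. A reader told that the trial had 90% power for 15 points will take a null as strong evidence against a benefit of that size. Whether that assurance holds depends on quantities the plan does not state.

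**Working it through.** **Inputs from the Sample size section.** Difference 15, SD 19, power 90%, alpha 5%, drop-out 20%. Sidedness is not stated; two-sided gives 34 and one-sided gives 28, so two-sided was used.

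**Step 1: reproduce the plan's figures.**

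n per group = 2 × (1.96 + 1.2816)² × (19/15)² = 33.7, rounded up to 34.

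Drop-out: 34/0.8 = 42.5, rounded up to 43 per group, 86 in total.

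Both match with a design effect of 1. The 9 extra athletes per group (43 − 34) are used up by drop-out and cannot also cover clustering.

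**Step 2: the slack in 34.** Rounding up leaves 34/33.717 = 1.008. Any design effect (DE) above about 1.008 takes power below 90%; two players per team with an ICC of 0.01 already gives 1.01. Power falls below 80% once DE exceeds 1.35.

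**Step 3: power under team randomisation.** With m players per team, DE = 1 + (m − 1) × ICC, the effective n is 34/DE, and

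power = Φ[(15/19) × √(34/(2·DE)) − 1.96].

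The difference detectable at 90% power is 15 × √(33.717 × DE/34). The document gives neither m nor ICC, so the values below are assumptions.

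| m | ICC | DE | Power, 34 per arm | Power, t on teams − 2 df | Evaluable per arm for 90% (total recruited) | Detectable at 90% |
|---|---|---|---|---|---|---|
| 1.5 | 0.05 | 1.025 | 89.5% | 88.2% | 35 (88) | 15.1 |
| 2 | 0.05 | 1.05 | 88.8% | 86.9% | 36 (90) | 15.3 |
| 3 | 0.10 | 1.20 | 84.4% | 80.8% | 41 (104) | 16.4 |
| 4 | 0.20 | 1.60 | 73.0% | 67.2% | 54 (136) | 18.9 |

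Worked row, m = 3 and ICC 0.10: DE = 1 + 2 × 0.10 = 1.20; effective n = 34/1.20 = 28.3; (15/19) × √(28.3/2) − 1.96 = 1.01; Φ(1.01) = 0.844.

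The team-based degrees of freedom are a conservative choice that the plan does not specify. The last two columns use the normal approximation.

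**Step 4: the possible offset.** If the model adjusted for baseline VISA-P and its correlation with the follow-up score were r = 0.5 (an assumption), the variance would be multiplied by 1 − 0.5² = 0.75.

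- m = 3, ICC 0.10: net factor 1.20 × 0.75 = 0.90, power about 93%.
- m = 4, ICC 0.20: net factor 1.60 × 0.75 = 1.20, power 84.4%.
- With this factor, 90% power holds up to a DE of about 1.008/0.75 = 1.34.

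**The case against.** The strongest reply is that the net error may be small or even favourable. The trial uses repeated measures and compares groups over time, while the sample size rests on a single raw SD. Adjustment for baseline VISA-P could more than pay for moderate clustering, as step 4 shows. This stands as a reason not to say that the true power is below 90%. It does not rescue the stated figure: the Sample size section takes no such credit and reports no data on the SD of change, and the Statistical analyses section does not clearly fix adjustment for baseline VISA-P.

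Second, athletes are recruited individually through association websites, e-mail, newspapers and tournaments, and then narrowed by eligibility criteria. Many teams could supply a single player, and the loss would then be trivial. This also stands as a limit on size. But randomising by team in order to prevent spill-over makes sense only if some teams are expected to supply more than one player.

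Third, the planned adjustment for type of sport and gender could remove some between-team variance and lower the relevant ICC. That is possible, and another reason to give a range.

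A reader might also infer that team-mates share a coach, a playing surface or a treatment location, and take a high ICC from that. The article states none of these. The point does not need them, since the analysis section itself allows for dependency. Nor is this an arithmetic slip: 34 and 43 are correct for individual randomisation. The planned multilevel analysis also means that nothing here shows an inflated false-positive rate.

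**Conclusion.** The point holds in this form: the stated 90% power rests on a formula that does not match team-level allocation, and on the plan's own inputs it is not supported. Without credit for baseline adjustment, the assumed combinations give power from 89.5% down to 73% (88.2% to 67.2% with team-based degrees of freedom). The lowest figures need four players per team and an ICC of 0.20, for which the document offers no evidence either way.

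A reader might conclude that the trial is underpowered, or that 86 athletes are too few. The documents do not establish that. Team size, ICC and the baseline correlation are all unstated, and plausible values put the net result on either side of 90%. What can be said is that the figure is not demonstrated for this design and should be restated.

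**What to change.** Keep 86 athletes and restate what that number delivers:

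- Give the expected number of teams and players per team.
- Apply DE = 1 + (m − 1) × ICC over a stated ICC range, saying where the range comes from.
- Include the 1 − r² factor only if adjustment for baseline VISA-P is fixed in the model, so that the restated power refers to the analysis that will be run.
- Replace the claim of 90% power with the resulting power, or with the difference detectable at 90%. Without baseline adjustment that difference is about 15.1 to 18.9 points over the assumptions above, against the 15 points called clinically relevant.

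The cost is a few sentences and possibly a less favourable headline figure. No extra athletes or visits are required.

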### Statistical analyses

Descriptive statistics (means and standard deviations, numbers and percentages) will be used to describe the characteristics of the intervention and control group and the outcome variables at the three measurement points. To evaluate potential group differences at the start of the study, baseline values will be analysed for differences between intervention group and control group. The effect of the ESWT treatment will be assessed using multilevel analysis. The multilevel analysis will be used to determine whether there is a difference on the primary and secondary outcome variables between the two groups over time. This statistical technique takes into account the dependency of observations of different subjects. Analyses will be adjusted for gender, age, type of sport, and baseline values of any other post hoc confounders. Analyses will be performed following the 'intention to treat' principle. Differences will be considered statistically significant at p < 0.05. All analyses will be done using SPSS version 16 (SPSS, Chicago, USA).

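### The covariate set of the primary VISA-P analysis is partly left to post hoc choice, and baseline VISA-P is not expressly among the fixed covariates

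*Protocol article*

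**What the plan says.** All statements below are in the protocol article.

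- **Covariates** (Statistical analyses): "Analyses will be adjusted for gender, age, type of sport, and baseline values of any other post hoc confounders". Three covariates are fixed and the rest, "baseline values of any other post hoc confounders", are open. The sentence covers all analyses, so it includes the primary one.
- **Primary outcome** (VISA-P questionnaire): "The primary outcome of the TOPGAME study is the self-reported VISA-P score". Baseline VISA-P is measured, but it is not listed by name among the covariates.
- **Baseline comparison** (Statistical analyses): "baseline values will be analysed for differences between intervention group and control group". The stated purpose is to look at possible group differences at the start. No test or threshold is given, and no use of the result is described.
- **Decision rule** (Statistical analyses): "Differences will be considered statistically significant at p < 0.05".

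No model with fixed covariates only is named as primary.

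**The concern.** A 5% test has its nominal error rate when the model is settled without reference to the results. Here the article says that some covariates will be identified after the fact. Adjusted estimates differ from one covariate set to another, so the primary estimate and p-value are not determined by the plan.

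The term confounder also fits poorly. Under random allocation, baseline differences between arms arise by chance. What makes a covariate worth including is how well it predicts the outcome, not how unbalanced it happens to be. Baseline VISA-P is the obvious predictor of later VISA-P, yet on this wording its inclusion is not secured.

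The pool of possible additions is wide: level and hours of sport, medical history and previous treatment, several VAS ratings and four ultrasound features. If, for illustration, ten independent candidates were each compared at 5%, the chance of at least one nominal difference would be 1 - 0.95^10 = 0.40. An occasion to add something is therefore likely to arise. At stake is whether a reader can trust that the primary result was not model-picked.

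**Working it through.** **1. The plan's own figure.** The Sample size section plans for a 15-point difference "with an SD of 19, a power of 90% and an alpha of 5%, 34 subjects per group are needed". Two-sided: n = 2 × (1.960 + 1.282)² × 19² / 15² = 33.7, so 34 per group. For 20% drop-out: 34 / 0.8 = 42.5, so 43 per group and 86 in total. Both figures reproduce. They use no covariate adjustment and do not change below.

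**2. Type I error under different selection rules.** The article gives no correlations, candidate list or rule, so these are assumptions. Common set-up: null simulation, 34 per arm, linear model, independent individuals.

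*Main setting: five candidates, correlation with outcome 0.5 (baseline VISA-P) and 0.2 (four others).*

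| Rule | Type I error |
|---|---|
| Baseline VISA-P fixed in advance | 4.6-5.1% |
| Add a covariate if its baseline p<0.05 | 3.5-4.0% |
| Same, with baseline VISA-P always in | about 4.5% |
| Most favourable of all subsets | about 14% |
| Same, with baseline VISA-P always in | about 10% |

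With 4,000 trials the simulation standard error of the 14% figure is √(0.14 × 0.86 / 4,000) = 0.0055, so it is good to about one percentage point.

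*Range over other assumptions: five candidates at 0.2, 0.3 or 0.4 each, or one candidate at 0.5 or 0.7; 10,000 trials each.*

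| Rule | Type I error |
|---|---|
| All covariates fixed in advance | 4.8-5.1% |
| Add if baseline p<0.05 | 3.0-4.4% |
| Add if baseline p<0.10 | 2.0-4.3% |
| Add if the estimate moves by 10% | 2.6-4.9% |
| Most favourable of unadjusted, each alone, all | 7.2-15.9% |

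Mechanical rules tend to be conservative: a predictor is left out exactly when it is well balanced, and the unadjusted standard error is then too large. Free choice works the other way.

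**3. Power, a separate question.** Unadjusted standard error of the difference: 19 × √(2/34) = 4.608 points. Adjusting for a baseline with correlation r multiplies it by √(1 - r²). Normal-approximation power is Φ(difference / SE - 1.96):

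| r (assumed) | SE | 10 points | 15 points |
|---|---|---|---|
| 0 (unadjusted) | 4.608 | Φ(0.210) = 58% | Φ(1.295) = 90% |
| 0.3 | 4.396 | Φ(0.315) = 62% | Φ(1.452) = 93% |
| 0.5 | 3.991 | Φ(0.546) = 71% | Φ(1.799) = 96% |
| 0.7 | 3.291 | Φ(1.079) = 86% | Φ(2.598) = 99.5% |

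Simulation with t-based tests at r = 0.5 gives slightly lower values: 57% unadjusted and 69% adjusted at 10 points; 89% and 95-96% at 15 points.

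**4. Does selection itself cost power?** At 10 points, selection by baseline p<0.05 gives 57%, the same as no adjustment. With baseline VISA-P forced in and the other four selected, power is 69%, the same as with baseline VISA-P alone. The gap comes entirely from whether baseline VISA-P is secured.

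**The case against.** Several stronger readings are tempting, and the article does not support them.

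- **That baseline tests choose the covariates.** The comparison of arms has its own stated purpose, and nothing links it to the adjustment sentence. It may feed the choice, but that is an inference. This stands.
- **That false positives are inflated.** Under strict selection on baseline differences the test is mildly conservative. The 14% figure assumes that every subset is fitted and the best reported. The text speaks of confounders, not of picking the most favourable model. This stands: 14% is an upper scenario, not a prediction.
- **That data-driven selection loses power.** It does not, as step 4 shows. At the planned 15 points, power stays near 90% even with selection.

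The simulations are also not this trial's analysis. They leave out the three fixed covariates, team-level allocation, the repeated measurements and the multilevel model, so the percentages are illustrations of scale. If the model takes baseline VISA-P as one of its time points, part of the power gain may already be there; the text does not settle this. Allocating whole teams makes chance imbalance more likely than individual allocation would, which is a fair reason to look at baseline data.

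Finally, a condensed article may leave candidate lists and selection rules to an analysis plan. That does not remove the point. The article does not merely omit a detail: it states that covariates will be chosen post hoc. An analysis plan that fixed the full set would contradict it.

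**Conclusion.** The point holds as a should-fix. The covariate set for the primary analysis is partly data-dependent by the article's own wording, so the 5% level is not assured. The direction of the error cannot be stated without the missing rule: about 4% under selection by baseline p<0.05, and up to about 10 to 14% if the most favourable model is freely chosen, with the lower figure applying when baseline VISA-P is always kept. Across all the rules and correlations tried, the span is about 2 to 16%. These figures rest on assumed correlations and candidate numbers and on independent individuals. Confidence is high for the wording and moderate for the size of the consequences.

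The failure to name baseline VISA-P is a second, related weakness. At an assumed correlation of 0.5 it is worth about 12 points of power for a 10-point effect (57% to 69%) and about 6 to 7 for the planned effect (89% to 95-96%). The planned sample size is not put in doubt on this account.

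**What to change.** In Statistical analyses:

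1. Delete the clause on post hoc confounders.
2. Name the covariates of the primary model: gender, age, type of sport and baseline VISA-P. For each secondary outcome, use its own baseline value in place of baseline VISA-P.
3. Present baseline characteristics by arm descriptively, and state that between-arm comparisons will not be used to select covariates.
4. Label any further adjustment as a sensitivity analysis that cannot replace the primary result.

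The cost is a sentence or two of analysis wording, with no change to sample size or conduct. It has to be settled before outcomes are examined by arm, because pre-specification cannot be recovered afterwards. The downside is that a chance imbalance in some other variable, which team-level allocation makes more likely, is then handled only in the sensitivity analysis.

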## Discussion

Despite its frequency and impact on athletic careers, and decades of research notwithstanding, management of patellar tendinopathy remains frustrating and unpredictable for both athletes and clinicians. ESWT appears to be a promising treatment method in patients with chronic patellar tendinopathy [11]. Up to now, only studies have been published in which ESWT has been used for the treatment of recalcitrant patellar tendinopathy in athletes who had several conservative treatments before and were finally referred to a sports medicine department for ESWT [11]. However, the effectiveness of ESWT has not been studied in the large group of athletes who continue sports participation with an early or mild symptomatic patellar tendinopathy. The TOPGAME study is the first RCT to study the effectiveness of patient-guided piezo-electrically generated ESWT in athletes with patellar tendinopathy who are still in training and competition. To our knowledge, it is also the first study that takes into account the training and competition load of the athletes using a web-based log.

This study will contribute to a better understanding of the effectiveness of ESWT as treatment for athletes with patellar tendinopathy who are still able to train and compete. By treating them at an early phase, we can get relevant information on whether it is possible to reverse or stop the progression of patellar tendinopathy, thereby preventing chronic impairment of athletic performance, work and daily activities.

